### 5.6. Statistical Analysis Plan

Statistical analysis will employ ANOVA with a repeated measures design and/or linear mixed model regression. The models will include baseline characteristics such as age, sex, prior fasting experience, and habitual dietary patterns as covariates. While our sample size is primarily powered for detecting changes in the primary outcome, we will conduct exploratory analyses of these potential modifying factors, acknowledging that subgroup analyses will be hypothesis-generating rather than definitive. Linear regression and/or general additive models will analyse the relationship between habitual dietary intake and baseline measures, as well as the magnitude of response to fasting. Additionally, correlation analyses will be conducted to evaluate the relationship between autophagic flux readouts and quantified molecular markers, aiming to identify potential biomarker candidates for future studies. Given the sample size, analyses stratified by factors such as sex, age groups, or physical activity levels will be considered exploratory and interpreted with appropriate caution.

Exploratory multi-omics outcomes will be integrated via a multi-step approach. First, each omics layer (e.g., metabolomics, proteomics, or transcriptomics) will be analysed independently using standard workflows. Integration will then proceed through: (1) correlation network analysis to identify associations between molecules across omics layers; (2) pathway enrichment analysis to uncover biological processes affected across these layers; and (3) machine learning approaches, including sparse partial least squares discriminant analysis (sPLS-DA), to identify key molecular signatures associated with changes in autophagic flux. Specifically, metabolomics data will identify altered metabolic pathways, which will be cross-referenced with proteomic changes in related enzymes and regulatory proteins. Additionally, changes in the gut microbiome will be correlated with plasma metabolites to identify potential microbe-derived metabolites. This integrated analysis aims to provide a systems-level understanding of fasting-induced molecular changes and their relationship to autophagic flux. Established multi-omics integration tools such as mixOmics and MOFA+ (Multi-Omics Factor Analysis) will be employed for the analysis.

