### 3.4. Baseline Visit

Consenting participants will be enrolled in the trial and undergo baseline clinical assessments, as outlined in Table 1 and Table 2. Following an overnight fast, participants will be screened by collecting medical, dietary, supplementation, and exercise history information and performing the Adult Pre-Exercise Screening System (APSS, 2019, version 2.0) assessment. Baseline evaluations will include the anthropometric measurements; collection of blood, urine, and stool samples; a buccal mucosa swab; an incremental VO_2_peak test on a cycle ergometer; and the completion of a wellbeing and symptoms questionnaire. Research volunteers will also receive instructions from a registered dietitian and study personnel for collecting a 10-day weighed food diary and adhering to fasting protocols. Continuous glucose monitor (CGM) along with a Fitbit device to monitor physical activity and sleep quality and duration will be also set up at baseline assessment.

**Table 1 nutrients-16-04297-t001:** Summary of the visit schedule.

Study Phase	Visit	Visit Title	Approximate Duration of the Visit	Notes
Screening	1	Screening evaluation	3 h	Medical history, blood sample, VO_2_peak test
Phase 1	2	Baseline assessment 1	2 h	Clinical measurements
	3	Start of fasting and cycling exercise/rest period	3.5 h	Fasting starts a night before
	4	End of fasting 1	2 h	Refeeding starts after this visit
	5	End of refeeding 1	2.5 h	4 days after of end of fasting visit
Phase 2	6	Baseline assessment 2	2 h	4 weeks after visit 4
	7	Start of fasting and cycling exercise/rest period	3.5 h	Fasting starts a night before
	8	End of fasting 2	2 h	Refeeding starts after this visit
	9	End of refeeding 2	2.5 h	4 days after of end of fasting visit
	10	Follow up assessment	4 h	4 weeks after visit 8

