### 5.5. Sample Size Calculation

A total of 25 volunteers will be recruited for the study. Given the crossover design, each participant will undergo both interventions, effectively creating two groups of 25. To estimate the required sample size, the change in LC3B-II to beta-actin ratio was considered. LC3B-II, the lipidated form of microtubule associated protein 1 light chain 3 beta that accumulates on autophagosomes when lysosomal degradation is blocked, is the gold standard marker for measuring autophagic flux in human samples [30]. Utilising ANOVA with a repeated measures design, assuming a standard deviation of 95.4, and aiming for 80% power at a significance level of 0.05, a difference of 30% (a change of 134.7 from a mean of 299.3 ng/mg protein/hour in the control group at baseline) could be detected with a sample size of 20 per group. Accounting for an estimated dropout rate of 20%, the initial recruitment target is set at 25 participants, based on the study by Bensalem et al. [29]. Sample size versus power plot is shown in Supplementary Figure S1. Additionally, sensitivity analyses, examining sample size requirements for detecting 20% and 40% changes, are shown. The exploratory outcomes will not be separately powered but will provide valuable hypothesis-generating data for future targeted studies.

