The implications of our findings extend beyond an individual’s health. With ageing populations globally, understanding how lifestyle interventions, including fasting, can promote cellular health and promote long-term health is paramount [39]. The PROFASTA trial could inform evidence-based recommendations for healthcare providers by establishing safety parameters, optimal timing, and monitoring requirements for combined fasting–exercise protocols. These findings may help develop practical guidelines for implementing fasting interventions in clinical settings and lifestyle programmes. Furthermore, this research aligns with growing evidence that emphasises the importance of personalised approaches to health interventions. Individual variations in metabolic responses to fasting and exercise highlight the need for tailored strategies that consider sex, age, genetic and epigenetic background, and lifestyle factors. By integrating insights from our study with the existing literature, we aim to contribute to the development of targeted fasting protocols that can be safely implemented across diverse populations to promote cellular and metabolic health.

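### Section 5.6 names stratification of about 20 completers by sex, age group or activity level but states no treatment-by-factor interaction, so as written it does not test effect modification and gives up power on continuous modifiers (minor)

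*Protocol article*

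**What the plan says.** Four statements in section 5.6 of the protocol article bear on this.

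- On the main models (repeated-measures ANOVA and/or a linear mixed model): "The models will include baseline characteristics such as age, sex, prior fasting experience, and habitual dietary patterns as covariates". No product of these covariates with the intervention is mentioned, and physical activity is not among the examples.
- On modifiers in general: "we will conduct exploratory analyses of these potential modifying factors, acknowledging that subgroup analyses will be hypothesis-generating rather than definitive". The form of these analyses is not given.
- On diet, including how it relates to the size of a person's response to the fast, a continuous method is named: "Linear regression and/or general additive models will analyse the relationship between habitual dietary intake and baseline measures, as well as the magnitude of response to".
- On sex, age and physical activity, the form named is strata: "analyses stratified by factors such as sex, age groups, or physical activity levels will be considered exploratory and interpreted with appropriate caution". The sentence gives the sample size as the reason for caution.

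Elsewhere, section 3.2 admits ages 18 to 70. Section 3.4 sets up a "Fitbit device to monitor physical activity and sleep quality and duration" at baseline. Section 5.5 sizes the trial so that the target difference "could be detected with a sample size of 20 per group", and then adds: "Accounting for an estimated dropout rate of 20%, the initial recruitment target is set at 25 participants". The Discussion says that individual variation in response to fasting and exercise serves to "highlight the need for tailored strategies that consider sex, age, genetic and epigenetic background, and lifestyle factors".

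**The concern.** Effect modification here means that the within-person B-A difference in autophagic flux changes with age, sex or activity. A separate analysis in each stratum estimates that difference several times, each time in a small group. It does not estimate or test how the difference changes between groups.

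Age is continuous over a span of 52 years, and activity may be as well. Cutting such a variable into groups treats everyone on one side of the cut as alike and discards the rest of the information. With 20 completers, two equal groups hold 10 people each.

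Two things are at stake in a hypothesis-generating analysis. A real gradient is more likely to be missed. And if a reader compares significance across strata, an effect that is the same for everyone can look specific to one group. The Discussion's interest in tailoring by sex, age and lifestyle makes such readings likely to be noticed.

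**Working it through.** **1. The plan's own sample size.** Inputs from section 5.5: SD 95.4, control mean 299.3, a 30% difference, 80% power, alpha 0.05 (taken as two-sided), 20% dropout.

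- 30% of 299.3 = 89.79.
- With zero within-person correlation, the SD of a paired difference is 95.4 × √2 = 134.9, so the standardised paired effect is 89.79 / 134.9 = 0.666.
- A paired t-test with n = 20 then has 80.6% power, so 20 is reproduced. 20 / (1 − 0.20) = 25 recruits is also reproduced.
- Section 5.5 also prints a change of 134.7. That is 134.7 / 299.3 = 45%, not 30%. This discrepancy is separate from the present point. It matters here only because it widens the range of effect sizes used in step 4.

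**2. Why a covariate alone does not test modification.** Write the response of person i under intervention j as

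y_ij = μ + period + τ·B_j + β·age_i + u_i + e_ij,

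where B_j is 1 for intervention B and 0 for A. In the B-A difference, β·age_i and u_i cancel. What remains is τ, a period term and error. The covariate therefore says nothing about whether the difference depends on age. With an added term γ·age_i·B_j, the difference becomes τ + γ·age_i plus the period term and error, and γ is the quantity wanted.

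**3. Power lost by grouping.** Assumptions, none of them given in the documents: n = 20, one B-A difference per person, a linear relation to the modifier with correlation r, two-sided alpha 0.05, no period term. The test of the slope on the continuous modifier is compared with the test between two halves split at the sample median (200,000 simulated trials per row; simulation error is roughly 0.1 point on each power).

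| Modifier | r | Continuous | Median split | Loss (points) |
|---|---|---|---|---|
| Normal | 0.2 | 13.4% | 10.1% | 3 |
| Normal | 0.3 | 25.2% | 16.9% | 8 |
| Normal | 0.4 | 43.1% | 27.8% | 15 |
| Normal | 0.5 | 64.1% | 42.2% | 22 |
| Normal | 0.6 | 83.6% | 59.9% | 24 |
| Uniform | 0.2 | 13.5% | 11.0% | 2 to 3 |
| Uniform | 0.3 | 25.4% | 19.2% | 6 |
| Uniform | 0.4 | 43.4% | 31.6% | 12 |
| Uniform | 0.5 | 65.4% | 48.6% | 17 |
| Uniform | 0.6 | 85.3% | 68.1% | 17 |

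The split used here already tests the two halves against each other. Separate within-stratum analyses would not even do that. Other cuts can lose more: up to about 26 points for three groups and about 29 for a 30/70 split. With r = 0 both tests reject in about 5% of trials, so the gain does not come from an inflated error rate.

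**4. Chance divergence between two halves.** Suppose the effect is the same for everyone and each half of 10 is tested by a paired t-test with power p. The chance that exactly one half is significant is 2p(1 − p).

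| Standardised paired effect | Source | p at n = 10 | Exactly one half significant |
|---|---|---|---|
| 0.66 | 80% power at n = 20 | 0.462 | 2 × 0.462 × 0.538 = 50% |
| 0.94 | 89.79 / 95.4 | 0.755 | 2 × 0.755 × 0.245 = 37% |
| 1.41 | 134.7 / 95.4 | 0.977 | 2 × 0.977 × 0.023 = about 5% |

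The last two rows read 95.4 as the SD of the within-person difference.

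**The case against.** The case on the other side has weight.

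- A reader might infer that stratification is the only method planned for modifiers. The text does not support that. The stratification sentence is a caution about interpretation, and the promised exploratory analyses of modifying factors have no stated form. A continuous intervention-by-age interaction could be among them, and an analysis plan that is not shown may specify it.
- A reader might infer that the trial will compare p-values between strata, or that it will use a median split. Neither is written. Both are assumptions used above to give a size.
- A reader might infer that activity is a continuous Fitbit measure. Section 5.6 does not name the source, and section 3.4 also collects an exercise history and a pre-exercise screening assessment.
- The plan already calls this work exploratory and gives no decision role to any stratum result. The Discussion's remark on tailoring is general. At weak modifier strength either method is inconclusive: at r = 0.3 even the continuous test has only about 25% power.

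All of this stands, and it limits the size of the point. It does not make grouping about 20 people a sound way to look for modification. An exploratory label governs how strongly a result is claimed, not whether the analysis addresses the question. The same section names a continuous method for diet but only strata for physical activity, so the better approach is already within its repertoire.

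**Conclusion.** The point holds as a minor one. Section 5.6 names strata for sex, age and activity and states no interaction. Strata alone do not test modification, and grouping a continuous modifier loses power in every scenario examined.

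The loss should not be read as a figure of this trial. It rests on an assumed modifier strength, distribution and split, and it is small if the modifier is weak. The conclusion is not sensitive to dropout: with all 25 recruits completing, the median-split loss is still about 3 to 5 points at r = 0.2 and 13 to 23 at 0.4 to 0.6. The chance-divergence figures apply only if someone compares significance between strata, and they fall steeply as the common effect grows.

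It would be wrong to conclude that the trial's main result is at risk. The primary B-A comparison does not depend on any of this.

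**What to change.** In section 5.6, replace the stratification sentence with wording such as:

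> Whether the B-A difference in autophagic flux varies with participant characteristics will be explored in the crossover model by adding one intervention-by-factor interaction at a time. Age will be kept continuous, as will physical activity where it is measured on a continuous scale; sex will be binary. Each interaction estimate will be reported with its 95% CI. Stratum-specific estimates will be given for description only, and significance will not be compared between strata. These analyses are exploratory.

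The cost is this change of wording, with no new data and no change to the primary analysis. The downside is that a linear term assumes a straight-line gradient. The additive models that 5.6 already names for diet can be used to check that. If the analysis plan already contains such an interaction, it is enough to align the article with it.

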### 5.3. Exploratory Outcomes

Several exploratory outcomes will also be examined:Levels of autophagy cargo receptor proteins in PBMCs such as p62/SQSTM1, NBR1, and OPTN;Calculated adjusted autophagy score based on (a) the primary outcome, (b) changes in PBMC pool make up, and (c) pre-existing data from cell type-specific autophagy calculated using flow cytometry;Plasma proteomics using Olink’s Proximity Extension Assay (PEA) technology to detect over 5400 proteins;Mass spectrometry-based proteomics and metabolomics of PBMCs;Plasma lipidomics and metabolomics;Detailed profiling of circulating immune cell populations and their functional states, along with molecular markers assessed via flow cytometry, including the lymphoid/myeloid ratio and a marker of protein acetylation in B cells;DNA methylation and genomic analysis in isolated PBMCs and buccal mucosa cells, including methylation-based ageing biomarkers such as DunedinPACE and GrimAge;Platelet characterisation involving proteomic analysis, flow cytometry, and activation assays to elucidate biochemical composition, surface marker expression, and functional responsiveness;Characterisation of plasma extracellular vesicles (EVs) using nanoparticle tracking analysis, transmission electron microscopy, and the proteomics of isolated EVs to determine size distribution, morphology, and cargo composition;Analysis of the gut microbiome through 16S ribosomal RNA (rRNA) gene amplicons and shotgun metagenomics.

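### The signature step in section 5.6 names a discriminant method (sPLS-DA) for a continuous target, change in autophagic flux; a continuous-response method would fit better

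*Protocol article*

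**What the plan says.** Section 5.6 (Statistical Analysis Plan) sets out three integration steps for the exploratory omics data. The third is "machine learning approaches, including sparse partial least squares discriminant analysis (sPLS-DA), to identify key molecular signatures associated with changes in autophagic flux". sPLS-DA is the only algorithm named in that step, though it is introduced as one example. The section then names mixOmics and MOFA+ as tools for the integrated analysis. Its first paragraph separately plans correlations between flux readouts and molecular markers, with biomarker candidates as their aim.

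Section 5.5 (Sample Size Calculation) shows the scale of flux. It refers to "a change of 134.7 from a mean of 299.3 ng/mg protein/hour in the control group at baseline", "assuming a standard deviation of 95.4". This is a rate on a continuous scale. The article gives no flux threshold, responder definition or other class label for the signature step. Section 5.5 also says that exploratory outcomes are not separately powered and serve to generate hypotheses.

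Section 5.3 (Exploratory Outcomes) gives an idea of the size of one omics layer: plasma proteomics uses a "technology to detect over 5400 proteins".

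**The concern.** The stated purpose and the named method do not match in scale. sPLS-DA finds combinations of features that separate groups fixed in advance. The question is which molecules go with a larger or smaller change in flux, and that change is a continuous quantity. Two ways of supplying labels are open, and each has a cost.

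- **Labels made by cutting flux change**, for example high against low. The result then depends on the cut, and differences in flux within each class are discarded. With about 20 completing participants there is little information to spare.
- **Labels taken from the design**, such as intervention A against B, or start against end of fasting. The method then fits its response, but it finds what differs between conditions. Any molecule that shifts with fasting will separate start from end, whether or not it moves with flux.

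At stake is how well the exploratory signature answers its own question. Choosing classes later, in a fuller plan, selects one of these two routes but does not remove the mismatch.

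**Working it through.** **1. The number of participants.** The article gives no figure for the signature step, so the relevant number is the evaluable sample in section 5.5. Inputs from that section are a 30% difference from a mean of 299.3, SD 95.4, and "aiming for 80% power at a significance level of 0.05" (two-sided assumed, since sidedness is not given).

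- 30% of 299.3 = 0.30 × 299.3 = 89.8.
- Two means, normal approximation: n per group = 2 × (1.96 + 0.84)² × (95.4 / 89.8)², about 17.7, rounded up to 18.
- Two-sample t: 19 per group.
- Paired t with zero within-person correlation: 20, with power 0.806.

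The stated result, "could be detected with a sample size of 20 per group", is therefore reproduced to within two. Dropout: 20 / (1 − 0.20) = 25, which agrees with "Accounting for an estimated dropout rate of 20%, the initial recruitment target is set at 25 participants". The reproduction uses 89.8. The printed change of 134.7 is 134.7 / 299.3 = 45% and gives only 8 to 10 by the same formulas. That is a separate matter and does not alter the point here. The signature step would have about 20 people, and at most 25.

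**2. What a cut would cost, if one were made.** Assumptions, none of them stated in the article: change in flux is normal, there is one value per person, the cut is at the median, and one marker is tested at a time without correction for multiplicity.

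- Splitting one of two jointly normal variables at its median multiplies their correlation by √(2/π) = 0.798.
- Relative information = 0.798² = 2/π = 0.637.
- Equivalent sample: 20 × 0.637 = 12.7; 25 × 0.637 = 15.9.

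**3. The same loss as power.** Simulation with 40,000 runs per row, n = 20, two-sided 0.05 test of one marker against flux change:

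| True correlation | Flux continuous | Flux split at median | Loss (points) |
|---|---|---|---|
| 0.4 | 0.43 | 0.28 | 15 |
| 0.5 | 0.64 | 0.42 | 22 |
| 0.6 | 0.84 | 0.60 | 24 |
| 0.7 | 0.96 | 0.79 | 17 |

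At n = 25 the pairs are 0.53 v 0.35, 0.75 v 0.52, 0.91 v 0.72 and 0.98 v 0.88.

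These figures show the price of dichotomising a single association. They do not measure the performance of a sparse multivariable classifier.

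**4. If design labels are used instead.** No arithmetic applies. Section 5.6 asks for signatures tied to change in flux, whereas a classifier trained on intervention or visit is never given flux as an input. Its output could be related to flux afterwards through the planned correlations, but the features would already have been chosen for another purpose.

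**The case against.** The case against has real weight, and several stronger readings that a reader might infer do not stand.

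- **That the plan commits to cutting flux.** It does not. The article mentions no median split, threshold or responder group, and the crossover supplies natural labels. The loss computed above is conditional on a choice that the article does not make.
- **That the biomarker aim rests on this step.** Section 5.6 assigns biomarker candidates to the correlation analyses, which involve no classes. The signature step adds to that aim but does not carry it.
- **That sPLS-DA is the sole method.** The word *including* leaves room for others, and mixOmics already contains the continuous-response version. The plan does not exclude the better choice.
- **That the number of features makes the classifier unsound.** More than 5400 proteins against 20 people is about 270 to 1 (5400 / 20), but the ratio is the same under sparse PLS regression. It is no argument for one method over the other.
- **That validation will be biased by splitting one person's records across folds.** No validation scheme is described, so this would be conjecture.

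It can also be said that class definitions and tuning belong in a fuller plan, and that an article need not give them. That is right as far as missing detail goes. What remains is that the text pairs a named method with a target whose scale does not suit it. The planned correlations relate flux to quantified markers and are not described as building a multivariable signature, so they do not fully replace this step.

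**Conclusion.** The point holds as a minor mismatch between method and target. For signatures of change in flux, section 5.6 names only a discriminant algorithm, while section 5.5 shows flux to be continuous. To run sPLS-DA, either flux must be cut or the labels must come from the design, and neither answers the stated question as directly as a method that takes flux as it is measured.

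The size can only be illustrated. Under a median split of normal data with one value per person, about 64% of the information is kept, so 20 participants count as about 13. For a single uncorrected marker with a true correlation of 0.4 to 0.7, power falls by about 15 to 24 points at n = 20. If design labels are used, there is no such loss, but the signature is one of condition.

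The consequence is confined to one exploratory, unpowered step. The primary outcome, the comparison of A with B, the sample size and the flux-marker correlations are untouched.

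**What to change.** In section 5.6, reword the third integration step:

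- For signatures of change in autophagic flux, use a continuous-response method such as sparse PLS regression in mixOmics, with change in flux as the response.
- State whether the association sought is within or between persons. Each participant completes both interventions and gives several blood samples, and a multilevel within-participant analysis removes differences between people, so the choice changes what the signature means.
- In any validation or tuning, keep all records of one participant together.
- Keep sPLS-DA for questions with true classes: intervention A against B, or start against end of fasting, and name the classes there.

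The cost is one reworded clause and a small amount of extra analysis. No new data, visits or software are needed.
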